## Abstract

**Background:**

Existing recommended treatment options for personality disorders (PDs) are extensive and costly. There is emerging evidence indicating that trauma-focused treatment using eye movement desensitization and reprocessing (EMDR) therapy aimed at resolving memories of individuals’ adverse events can be beneficial for this target group within a relatively short time frame. The primary purpose of the present study is to determine the effectiveness of EMDR therapy versus waiting list in reducing PD symptom severity. Furthermore, the effects of EMDR therapy on trauma symptom severity, loss of diagnosis, personal functioning, quality of life, and mental health outcomes will be determined. In addition, the cost-effectiveness of EMDR therapy in the treatment of PDs is investigated. Moreover, predictors of treatment success, symptom deterioration and treatment discontinuation will be assessed. Lastly, experiences with EMDR therapy will be explored.

**Method:**

In total, 159 patients with a PD will be included in a large multicentre single-blind randomized controlled trial. The Structured Clinical Interview for DSM-5 Personality Disorders will be used to determine the presence of a PD. Participants will be allocated to either a treatment condition with EMDR therapy (ten biweekly 90-min sessions) or a waiting list. Three months after potential treatment with EMDR therapy, patients can receive treatment as usual for their PD. All participants are subject to single-blinded baseline, post-intervention and 3-, 6- and 12-month follow-up assessments. The primary outcome measures are the Assessment of DSM-IV Personality Disorders and the Clinician-Administered PTSD Scale for DSM-5. For cost-effectiveness, the Treatment Inventory of Costs in Patients with psychiatric disorders, EuroQol-5D-3L, and the Mental Health Quality of Life Questionnaire will be administered. The PTSD Checklist for DSM-5, Brief State Paranoia Checklist and Difficulties in Emotion Regulation Scale will be used to further index trauma symptom severity. Type of trauma is identified at baseline with the Childhood Trauma Questionnaire-SF and Life Events Checklist for the DSM-5. Personal functioning and health outcome are assessed with the Level of Personality Functioning Scale-BF 2.0, Outcome Questionnaire-45 and Mental Health Quality of Life Questionnaire. Experiences with EMDR therapy of patients in the EMDR therapy condition are explored with a semi-structured interview at post-intervention.

**Discussion:**

It is expected that the results of this study will contribute to knowledge about the effectiveness, and cost-effectiveness of trauma-focused treatment using EMDR therapy in individuals diagnosed with a PD. Follow-up data provide documentation of long-term effects of EMDR therapy on various outcome variables, most importantly the reduction of PD symptom severity and loss of diagnoses.

**Trial registration:**

Netherlands Trial Register NL9078. Registered on 31 November 2020

Committees	Data will be processed in a data management system (Research manager), which facilitates monitoring. Via this system an Audit-trial will be created and a monitor will be assigned. Independently from the researchers and sponsor, this person will monitor the study via the research manager data management system. Furthermore, the monitor will visit the site with a minimum frequency of one visit per year. After the study, a close-out visit will be planned. The monitor will check whether study procedures are followed correctly, and will check the study site's documentation, the participants' source data, electronic Case Report Form (eCRF) entries, and the correct maintenance of the Investigator Site File. At the site, monthly research meetings take place. In these meetings, the project will be discussed with the steering committee. Furthermore, the sponsor will submit progress and safety reports to the Medical Research Ethics Committee (MREC) once a year, informing them of the numbers of inclusions and completions, adverse reactions and other important information concerning the safety of patients. According to the guidelines on data monitoring committees [26], a Data Monitoring Committee (DMC) might not be implemented in studies with non-critical indications or when the intervention under investigation is characterized and known for not harming patients. EMDR therapy is an evidence-based treatment for PTSD and has been found to be safe in patients with a personality disorder. A (DMC) is therefore not instituted.

## Introduction

Patients diagnosed with a personality disorder (PD) often report that they were exposed to adverse childhood events [7]. Most studies in this area include patients with borderline personality disorder (BPD) of which many experienced verbal (72%), physical (46%) and sexual (26%) abuse [72]. A recent study showed that 97% of BPD patients reported at least one type of childhood trauma, including abuse and neglect [56]. In other types of PDs, rates of childhood maltreatment are high as well, with 73% reporting abuse and 82% neglect [7]. Therefore, it is no surprise that prevalence rates of posttraumatic stress disorder (PTSD) among PDs are high, ranging from 41 to 56% in BPD patients [56, 71] and from 20 to 47% in patients with other PDs [29, 70, 71]. Also, prospective research has established associations between childhood maltreatment and development of PDs. For example, data from the longitudinal Children in the Community Study showed that adverse childhood experiences significantly predicted the development of a PD in later life (OR = 6.83) [15, 36, 39, 40]. Taken together, these results point to the importance of adverse childhood experiences and their influence on the development and severity of PD symptoms later in life.

Due to impairments in cognition, emotion regulation and impulse control [44], PD patients experience reduced interpersonal functioning, quality of life and subjective well-being [18]. In a large sample of PD patients, severe impairments in quality of life were found, comparable to the burden associated with rheumatic diseases, lung cancer and Parkinson’s disease [60]. Furthermore, longitudinal evidence suggests that adolescent PDs predict dysfunctional outcomes (e.g. social impairment, suicide, violence) later in life [17]. More specifically, cluster A symptoms were found to be significantly related to a delayed formation of residential, career, financial, romantic and family roles [16, 17], cluster B symptoms to adult aggressive, criminal, impulsive and self-destructive behaviour [38, 17], while cluster C symptoms predicted suicide attempts and partner conflict in early adulthood [14, 37, 17]. Besides these adverse effects stemming from the presence of PDs, a large proportion of individuals with PD are diagnosed with comorbid mental health conditions (67––97% [44]) that exert additive negative effects on functional outcome measures [19]. It is therefore understandable that societal costs of PDs are high (e.g. estimated €11,126 over 1 year prior to treatment [59]). Particularly the recommended treatment options for BPD proved to be extensive and costly [51]. To illustrate, in eight systematically reviewed randomized controlled trials (RCTs) [51], the mean duration of various PD treatments ranged from 168 [41] to 504 days (Bateman, [6]), with an average of 358 treatment days per patient. Moreover, such extensive treatment tracks require (partial) hospitalization or multiple appointments per week [51], further increasing intervention costs.

It has been argued that societal costs of PDs could be greatly reduced by treating this patient group [25]. For example, in 24 patients admitted for treatment at a mental health hospital, a reduction per patient was found involving in-patient, out-patient and prison costs, from £13,966 over 1 year prior to treatment to £1,308 over 1 year following discharge from treatment [25]. Although it is not clear from the description of this study how long and costly these treatments were, these results suggest that if there are good, targeted treatments that can alleviate the symptoms of PD, this would not only curb personal suffering but also reduce and prevent societal costs.

In this regard, there is hope on the horizon. Evidence suggests that (trauma-focused) psychotherapies of short duration might be effective in the treatment of PDs. For example, a recent meta-analysis demonstrated a strong decline in BPD symptoms (Hedges’ *g* = .52), when PTSD patients with comorbid BPD were treated with 4 to 25 sessions of trauma-focused therapies lasting 50 to 120 min [58]. Two studies used treatment with eye movement desensitization and reprocessing (EMDR), a therapy of first choice for PTSD [9, 32, 69]. In treating PTSD, EMDR therapy has been found to be well tolerated and cost-effective [21, 24, 48, 49]. Furthermore, an uncontrolled study showed that a median of four sessions of EMDR therapy was beneficial and safe in patients with comorbid PD and PTSD, where no difference in efficacy of EMDR therapy was found between patients with BPD and other PDs [57]. The effectiveness of EMDR therapy on PD symptom severity has also been studied in samples of patients with PDs but without a PTSD diagnosis. For instance, the results of a RCT comparing five sessions of EMDR therapy to a waiting list in patients diagnosed with any PD, but without PTSD, revealed medium to large effect sizes for psychological symptoms (Cohen’s *d* = .65), psychological functioning (Cohen’s *d* = .62) and personality functioning (Cohen’s *d* = .56), without the occurrence of adverse events [33]. These findings are particularly important because the length of treatment was brief in that patients received a mere total of 7.5 h of EMDR therapy. Yet, gains were maintained at three-month follow-up [33]. The findings of a recent study support the notion that treatment duration of PDs, like BPD, can even be shorter. It was found that a significant reduction of BPD symptoms was established, using a combination of EMDR therapy and prolonged exposure. Interestingly, one third of the patients lost their positive screen for BPD post-treatment after only eight treatment days [22]. These results suggest that EMDR therapy can be effectively, safely and more affordably applied to treat symptoms of PDs. However, until now, studies regarding the effects of EMDR therapy for the symptoms of PDs are limited to open label trials. Accordingly, the next step is to perform an RCT comparing the effectiveness of EMDR therapy versus no treatment intended to control for spontaneous recovery.

Even if we are able to determine that a large proportion of patients with PD can be helped with good treatment, it is still important, for improvement of treatment and cost-effectiveness, to understand which factors predict treatment success and discontinuation. To this end, several predictors have already been identified. Namely, a systematic review showed that, in patients with a PD, higher pre-treatment symptom severity and patient-rated therapeutic alliance significantly predicted greater symptom reduction [5]. Another review found that 37% of 2516 PD patients discontinued treatment which was associated with a series of patient characteristics including younger age, lower education, lower occupational levels, amount of PD diagnoses/criteria, worse general functioning and substance use [50]. In addition, a recent study found that patients with more severe childhood physical abuse were significantly more likely to discontinue treatment [3]. Unfortunately, one of the major problems with this extensive list of predictors is the lack of replication [3]. Additionally, predictive factors of therapy success and discontinuation of EMDR therapy for patients with a PD have not yet been investigated. Thus, in short, while these findings are indicative, they are certainly not conclusive.

To fill these gaps in the literature, the present study, the Trauma-focused EMDR for Personality disorders among Outpatients (TEMPO) study, will be conducted. The purpose of this study is to determine the effectiveness of EMDR therapy in comparison to a waiting list control condition in reducing PD symptom severity in a sample of patients diagnosed with a PD. Furthermore, the effects of EMDR therapy on trauma symptom severity, loss of diagnosis, personal functioning, quality of life and mental health outcomes will be determined. In addition, the cost-effectiveness of EMDR therapy in the treatment of PDs is investigated. Moreover, predictors of treatment success and dropouts will be assessed. Lastly, experiences with EMDR therapy will be explored.

## Method

### Design

The TEMPO study is a single-blind randomized controlled superiority trial with two arms, i.e. EMDR therapy and waiting list. The trajectory of a participant through the study is shown in Fig. 1. The experimental group will receive ten bi-weekly EMDR sessions of 90 min each, with a total duration of 15 h of treatment over 5 weeks. The groups are compared at baseline (pre-randomization; T0), post-intervention (after 5 weeks; T1), 3-month (T3), 6-month (T6) and 12-month (T12) follow-up. At baseline, demographical data will be collected for predictive analyses of treatment success and treatment dropout. At T1, patient dropout will be recorded and a random selection of patients in the experimental condition will be interviewed to assess their experiences with EMDR therapy. Until T3, patients do not receive further treatment, except in a crisis situation. At T3, all patients will be invited by their therapist for a consultation to examine whether (further) treatment is necessary. Any available treatment, except EMDR therapy, will be offered. At T12, when participation is concluded, control patients will also be offered the opportunity to receive EMDR therapy.

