### Sample size calculation

In order to test the effectiveness of EMDR in reducing the number of PD symptoms over time, relative to waiting list, a linear mixed model (LMM) with intention-to-treat will be used. A RCT of five EMDR sessions revealed an effect size of .65 for change in psychological symptoms, .62 for psychological functioning and .56 for change in personality functioning [33]. Since change in personality functioning is also (primarily) assessed in the current study, although with the aid of a different measure (Assessment of DSM IV Personality disorders; ADP-IV), the effect size for the main analysis is expected to approximate the effect size found by Hafkemeijer et al. [33]. With the aid of standardization by post score standard deviations (standard procedure for meta-analyses), this effect size decreases to .46. Therefore, an effect size of .43 was estimated to be appropriate for this study. Using Liu and Liang’s [45] equation, assuming a correlation of .7 between five repeated measurements, a treatment effect size of .43, a power of .8, an *α* significance level of .05, and two treatment conditions, the power analysis resulted in a total sample size of 132 patients. With an estimated dropout rate of 20%, a total of 159 patients is needed.

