Predictors of treatment success and discontinuation will be separately assessed with logistic regression analyses and calculated with 5000 bootstraps. Treatment success is defined as a loss of PD diagnosis at T1 in a first analysis, and at T12 in a second analysis. Considering the literature (see introduction [5]) and to test whether effectiveness differs between specific PDs, patients with or without PTSD, the centres of treatment and the EMDR therapists, the following predictors will be entered into a backward logistic regression with a two-tailed significance level of *α* = .05 as criterion: (1) pre-treatment symptom severity, (2) patient-rated therapeutic alliance, (3) specific PS diagnosis, (4) PTSD diagnosis, (5) centre of treatment and (6) EMDR therapist. Considering the literature (see introduction [50, 61]) and to test whether discontinuation differs between specific PDs, patients with or without PTSD, the centres of treatment and the EMDR therapists, the following potential predictors of treatment discontinuation will be entered into a backward logistic regression with a two-tailed significance level of *α* = .05 as criterion: (1) treatment credibility, (2) age, (3) education, (4) occupational levels, (5) amount of PD diagnoses, (6) amount of PD criteria, (7) general functioning, (8) substance use, (9) severity of adverse childhood events, (10) specific PS diagnosis, (11) PTSD diagnosis, (12) centre of treatment and (13) EMDR therapist. Analyses will be checked for robustness by redoing them with survival analysis.

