In conclusion, the present study is the first RCT that will determine the effectiveness of EMDR therapy in reducing PD symptom severity and its ability to make patients no longer meet the diagnostics criteria of their PD at 1-year follow-up. If EMDR therapy indeed proves to be (cost-)effective in reducing or abolishing PD symptoms, this would provide a strong argument for including EMDR therapy as a standard treatment option for PDs, thereby significantly reducing treatment duration and costs, evidently benefiting the individual and society at large.

Protocol version 2, 29-11-2021

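### EMDR versus waiting list can be estimated only up to T3, but the sample size, the T12 success definition and the 1-year claim treat T6 and T12 as the same comparison

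*Protocol article*

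**What the plan says.** The Introduction of the protocol article gives the purpose as EMDR against a waiting-list control for PD symptom severity, and describes the intended comparison as EMDR against no treatment, to allow for spontaneous recovery.

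Under Design, no further treatment is given before T3 except in a crisis. At T3 all patients are seen by their therapist and "Any available treatment, except EMDR therapy, will be offered". The Conditions section names emotion regulation training, schema therapy and dialectical behaviour therapy as examples. It adds that controls are registered by intake date, so that they wait no longer than they otherwise would. EMDR is offered to controls only at T12.

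On the main analysis, Sample size calculation says "a linear mixed model (LMM) with intention-to-treat will be used". The power inputs are "assuming a correlation of .7 between five repeated measurements", a single effect ("an effect size of .43 was estimated to be appropriate for this study") and 80% power, and "the power analysis resulted in a total sample size of 132 patients". Analyses adds only that mixed models by intention to treat will be used. No primary visit is named.

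For the predictor analyses, "Treatment success is defined as a loss of PD diagnosis at T1 in a first analysis, and at T12 in a second analysis". The closing paragraph of the Discussion says that "the present study is the first RCT that will determine the effectiveness of EMDR therapy in reducing PD symptom severity", and extends this to loss of diagnosis at one year.

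**The concern.** Two of the four post-baseline visits, T6 and T12, fall after other PD treatment becomes available in both arms. At those visits the randomised contrast is EMDR followed by optional usual care against delayed optional usual care. That is a legitimate question, but it is not the one in the statement of purpose.

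The Discussion hypothesises that further treatment will be shorter after EMDR. If so, controls receive more active treatment after T3, and if that treatment works the difference between arms narrows. An effect averaged over all visits would then mix two questions and understate EMDR against waiting list.

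The T12 success definition has a different problem. A patient who loses the diagnosis after up to nine months of other PD therapy (T3 to T12) counts as a treatment success. The predictors listed include the EMDR therapist and the therapeutic alliance, which suggests an analysis within the EMDR arm, with no comparator to separate the two sources of improvement.

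**Working it through.** **Inputs from Sample size calculation:** d = 0.43, ρ = 0.7, m = 5 measurements, power 0.80, α = 0.05, total 132. The sidedness of α is not stated there; two-sided is used because one-sided gives 102 and does not fit.

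**1. Reproducing 132.** Liu–Liang formula with exchangeable correlation:

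n per arm = 2(z₀.₉₇₅ + z₀.₈₀)² [1 + (m − 1)ρ] / (m d²), with (1.960 + 0.842)² ≈ 7.849.

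- m = 5: 2 × 7.849 × 3.8 / (5 × 0.1849) = 64.5, so 65 per arm, 130 in total. A t-based version gives 66 per arm, exactly 132.
- m = 4: 2 × 7.849 × 3.1 / (4 × 0.1849) = 65.8, so 66 per arm, 132 in total.
- m = 2 (T1 and T3 only): 72.2, so 73 per arm, 146 in total.
- m = 1: 84.9, so 85 per arm, 170 in total.

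The stated figure is reached only if T6 and T12 count with the same 0.43 as T1 and T3.

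**2. Mean effect if it shrinks after T3.** Let f be the fraction of 0.43 that remains at T6 and T12. The documents give no value, so f is an assumption and is shown as a range. Mean over the four post-baseline visits = 0.43 × (2 + 2f)/4.

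**3. Power of that average with 66 per arm.** Power = Φ(d̄ / √(2v/66) − 1.96).

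- Unadjusted, as in the protocol's formula with m = 4: v = (1 + 3 × 0.7)/4 = 0.775.
- Adjusted for baseline, with baseline also correlated 0.7: v = 0.775 − 0.7² = 0.285.

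| f | Mean effect | Power, unadjusted | Power, baseline-adjusted |
|---|---|---|---|
| 1 | 0.430 | 80% | >99% |
| 0.75 | 0.376 | 69% | 98% |
| 0.50 | 0.323 | 56% | 93% |
| 0.25 | 0.269 | 42% | 82% |
| 0 | 0.215 | 29% | 64% |

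T0 is left out of these averages. Including it with zero effect would lower the mean to 0.344 and power to about 62% (v = 0.76) even at f = 1. That is a separate matter and should not be counted here.

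**4. Power of a contrast before other treatment opens, d = 0.43.**

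- T3 alone, unadjusted, 132 patients: v = 1, 0.43/√(2/66) = 2.47, power about 70%.
- T3 alone, baseline-adjusted, 127 patients (159 × 0.8): v = 1 − 0.49 = 0.51, 0.43/√(2 × 0.51/63.5) = 3.39, power about 92%.
- T1 and T3 together, 132 patients: unadjusted v = 0.85, about 76%; adjusted v = 0.36, about 98%.

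**5. Like for like.** At 127 patients with baseline adjustment, the four-visit average has about 93% power at f = 0.5 and about 62% at f = 0, against 92% for T3 alone. At half retention, restricting to T3 gains no power; it gains a clear estimand.

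**The case against.** Three points on the other side carry weight.

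First, a reader might infer that the main test pools T6 and T12 with the earlier visits. The article does not state this. Pooling is implied by the power calculation, but Design says that the groups are compared at each visit, which fits visit-specific contrasts from the same model. The full protocol or an analysis plan may already specify them. So the power figures are conditional on an averaged test.

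Second, a reader might infer that the 1-year comparison is invalid. It is not. Allocation is random, analysis is by intention to treat, and controls are not offered EMDR before T12. The T12 contrast is therefore a valid comparison of two strategies, and it suits the societal cost-effectiveness question. What it cannot show is EMDR against no treatment at one year.

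Third, the Discussion acknowledges that treatment after T3 may differ considerably between patients, presents this as unavoidable on ethical grounds, and says that care use will be recorded so that differences between arms can be explored. That is fair disclosure. It does not change the main contrast, the success definition or the concluding claim.

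The T12 success definition belongs to a predictor analysis and not to the effectiveness test. That limits its weight, but the definition is fixed in the text and would not be cured by detail elsewhere.

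**Conclusion.** The point holds and should be fixed. EMDR against waiting list is identified at T1 and T3 only. The sample size applies the same effect beyond that period, no primary visit is named, and the T12 success definition and the concluding 1-year statement credit EMDR with results that may include other treatment.

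If the test is the average over visits, the mean effect falls from 0.43 to between 0.376 and 0.215 as the retained fraction goes from 75% to 0%. Unadjusted power falls from 80% to between 69% and 29%; with baseline adjustment it lies between 98% and 64%. These figures rest on the protocol's 0.43 and 0.7, on 66 analysed per arm, and on retained fractions that are assumed. They do not support a flat statement that the trial is underpowered: with baseline adjustment, power stays above 80% unless less than about a quarter of the effect remains. The shift in what is estimated occurs whichever model is used.

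**What to change.** - **Primary contrast.** Name a visit-specific, baseline-adjusted contrast before other treatment opens, either T3 or T1 and T3 together, estimated from the mixed model fitted to all visits. Both choices are defensible; one must be fixed in advance. State the baseline adjustment explicitly, because T3 alone has about 92% power at 127 patients with it and only about 70% at 132 without it.
- **T6 and T12.** Report them as a secondary randomised comparison of EMDR followed by optional usual care against delayed usual care.
- **Success definition.** Use loss of diagnosis at T3 as the second definition, or keep T12 and label it as diagnosis status after EMDR plus any later treatment.
- **Discussion.** Reword the concluding statement so that the 1-year result is a comparison of strategies and not an effect of EMDR against no treatment.

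The cost is wording in Sample size calculation, Analyses and Discussion. No visit, patient number or treatment offer changes. The downside is that the 1-year result becomes secondary.
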